#### 6.4. Dosage and administration of study vaccine

The immunization schedule consisted of two vaccinations, at least 21-day apart, at the same dose. There are two dosage regiments in this study. Subjects will be injected with 0.25 ml or 0.5 ml vaccine, with aluminium (AlPO4) adjuvant, intramuscularly (i.m.) in the deltoid of the non-dominant arm ([Table 6-2](#)).

**Table 6-2 Dosage and administration of study vaccine:**

| Group | Dosage  | Content       |                            |
|-------|---------|---------------|----------------------------|
|       |         | Total protein | Adjuvant AIPO 4 |
| A05   | 0.25 ml | 5 µg          | 150 µg                     |
| B10   | 0.5 ml  | 10 µg         | 300 µg                     |

The subjects will be observed closely for at least 2 hours following the administration of study vaccines, with appropriate medical treatment readily available in case of a rare anaphylactic reaction.

## 6.5. Concomitant treatment

The investigator should instruct the subject to notify the study site about any new medical treatment he/she takes during study period. All vaccines, medications, both permitted and non-permitted, and significant non-drug therapies, such as surgery, physical therapy and blood transfusions, administered during the 210-day study period must be listed on the Concomitant Treatment logs of Case Report Form. Those records may include generic name / trade names (allowed for combination medication only), medical indication, total daily dose, route of administration, start and end dates of treatment

The prior treatment of investigational products, other vaccine(s), immunoglobulins/blood products, immunosuppressants/immunomodulators and acetylsalicylic acid should be checked for enrollment criteria (see [Section 4.2.2](#)). All treatments administered 30 days prior to first vaccination should be recorded in the CRF.

All concomitant medications administered for the treatment of an adverse event, at any time, must be recorded as well.

### 6.5.1. Permitted treatment

Any treatments other than those prohibited in [Section 6.5.2](#) may be administered during this trial. These may include but not limit:

- ◆ Inhaled and topical steroids
- ◆ Oral contraceptives
- ◆ Vitamins and dietary supplements\*

\* The administration of both vitamins and dietary supplements do not have to be recorded in the CRF.

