##### **2. Prohibited:**

- (1) The following treatments are prohibited until 30 days after the second vaccination:
  - Other vaccine
  - Immunoglobulins
  - Any blood products
  - Immunosuppressants or other immunomodulators\*

\* For corticosteroids, this includes prednisone  $\geq 0.5$  mg/kg/day or equivalent.

Inhaled and topical steroids are allowed.

- Chronic or long-term (defined as > 14 days) use of acetylsalicylic acid medication

(2) The following treatments are prohibited during the study period:

- Investigational/non-registered product (including drug, vaccine and invasive medical device)

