### 6.5.2. Prohibited treatment

The following medications are prohibited during this clinical study:

- (1) The following treatments are prohibited until 30 days after the second vaccination:
  - Other vaccine
  - Immunoglobulins

- Any blood products
- Immunosuppressants or other immunomodulators\*
  - \* For corticosteroids, this includes prednisone  $\geq 0.5$  mg/kg/day or equivalent. Inhaled and topical steroids are allowed.
- Chronic or long-term (defined as  $> 14$  days) use of acetylsalicylic acid medication

(2) The following treatments are prohibited during the study period:

- Investigational/non-registered product (including drug, vaccine and invasive medical device)

Subjects who have received these prohibited treatments should be withdrawn from this trial.

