## **6.6. Rescue medication**

Rescue medication defined as drugs used to control symptoms that are induced post-vaccination could be administrated based on the investigator's contemplation. Use of rescue medication must be recorded on CRF.

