**Table 7-1 Solicited local and general symptoms /adverse events:**

| Solicited local (at injection site) AEs                                                                                                                                                                                                                   | Solicited general AEs                                                                                                                                                                                                                   |
|-----------------------------------------------------------------------------------------------------------------------------------------------------------------------------------------------------------------------------------------------------------|-----------------------------------------------------------------------------------------------------------------------------------------------------------------------------------------------------------------------------------------|
| 
 
○ Pain at the injection site
 
○ Tenderness at the injection site
 
○ Redness at the injection site
 
○ Swelling at the injection site
 
○ Ecchymosis at the injection site
 
 | 
 
○ Fever*
 
○ Nausea/Vomiting
 
○ Diarrhea
 
○ Appetite loss
 
○ Headache
 
○ Myalgia
 
○ Joint pain
 
○ Fatigue
 
○ Shivering
 
 |

---

\* Oral temperature will be recorded in the evening. Should additional temperature measurements be performed at other times of day, the highest temperature will be recorded.

The oral temperature will be monitored every evening until 6 days after each vaccination. If it has been measured for more than one time, only the highest level should be recorded in the diary card. Subjects with an oral temperature  $\geq 37.5^{\circ}\text{C}$  will be defined as fever.

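### Fever is counted without regard to antipyretic intake, and the time of intake is not linked to the reading, so reported fever at each dose can be understated by an unknown amount

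*Protocol*

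**What the plan says.** **What may be taken.** Protocol Section 6.5.1 says that treatments not prohibited in Section 6.5.2 "may be administered during this trial. These may include but not limit", and then gives three examples, none of them an analgesic. The one relevant entry among the prohibited treatments (Synopsis Section IX, repeated in Section 6.5.2) is "Chronic or long-term (defined as > 14 days) use of acetylsalicylic acid medication". Section 6.6 adds: "Rescue medication defined as drugs used to control symptoms that are induced post-vaccination could be administrated based on the investigator's contemplation". Nothing addresses preventive use before a dose.

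**How fever is measured.** The text with Table 7-1 states: "The oral temperature will be monitored every evening until 6 days after each vaccination". If a subject takes further readings, the highest is the one recorded. Table 7-2 sets fever at 37.5°C or above and grades it on temperature alone.

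**What is recorded about drugs.** Section 6.5 requires all medication over the 210 days to be listed. The fields it names, introduced as ones that may be included, end with "medical indication, total daily dose, route of administration, start and end dates of treatment". Section 6.6 is firm on rescue drugs: "Use of rescue medication must be recorded on CRF". Section 7.3.5 asks for the treatment given for each adverse event.

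**What it feeds.** Section 9.1 makes the percentage and intensity of local and systemic symptoms at each dose a primary endpoint. Section 10.3.2 analyses these descriptively, with counts, percentages and 95% confidence intervals per dose and overall.

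**The concern.** Analgesics and antipyretics act directly on several solicited symptoms: fever, injection-site pain, headache, myalgia and joint pain. A subject who takes an antipyretic in the afternoon and reads 37.3°C that evening is recorded as afebrile, exactly like an untreated subject with the same reading. Without the time of intake, nobody can later tell the two apart.

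At stake is the meaning of the fever percentage at 5 µg and 10 µg. It would describe fever as it appears with whatever medication subjects chose to take, but it would be read as the vaccine's reactogenicity. The intensity of pain-type symptoms is affected in the same direction, though less, because a treated headache has still occurred and can still be recorded. Intake times that are never collected cannot be recovered by a later analysis plan.

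**Working it through.** The protocol has no figure to reproduce. Section 10.6 marks sample size as not applicable, and Section 10.3.2 plans no hypothesis. The check has two parts.

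**1. Does the existing recording close the gap?**

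- *Dates and indication:* foreseen in Section 6.5. They show on which day a drug was used and why.
- *Time of day:* not named. With one required reading per day, dates cannot place a tablet before or after that reading.
- *Diary:* Sections 7.3.4 and 7.3.5.1 describe temperature and symptoms. No medication item is mentioned.
- *When medication is next recorded at a visit:* after dose 1, at Visit 3, Day 14–17 (Section 5.4). After dose 2, at Visit 5, Day 39–45 (Section 5.7.1). Dose 2 falls on Day 21–24, so the gap is 39 − 24 = 15 days at the shortest and 45 − 21 = 24 days at the longest. No medication question is specified for the 7-day telephone contact. Subjects are told to notify the site of new treatments, but a single tablet may otherwise rest on recall two to three weeks later.

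**2. How large could the effect be?**

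Input from the protocol: Table 6-1 gives A05 = 1 + 1 + 3 + 25 = 30 and B10 = 1 + 4 + 25 = 30. Every rate below is an assumption.

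*Simple illustration.* Let p be the true share of subjects with fever and f the share of febrile subjects left with no qualifying reading. The observed rate is p(1 − f). With p = 20% (6 of 30):

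- f = 25%: 6 × 0.75 = 4.5 of 30, or 15%
- f = 50%: 6 × 0.50 = 3 of 30, or 10%

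*Wider range.* Let u be the share of subjects using such a drug in the window and m the share of their events masked. The observed rate is p(1 − u·m). Take u from 10% to 50% and m from 30% to 80%. The relative loss u·m then runs from 0.10 × 0.30 = 3% to 0.50 × 0.80 = 40%.

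| True rate | Smallest loss (3%) | u = 30%, m = 50% (15%) | Largest loss (40%) |
|---|---|---|---|
| 10% | 9.7% | 8.5% | 6.0% |
| 20% | 19.4% | 17.0% | 12.0% |
| 50% | 48.5% | 42.5% | 30.0% |

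The chance of seeing no fever at all in 30 subjects when the true rate is 10% is 0.90^30 = 4.2% without masking, 0.915^30 = 7.0% in the middle case, and 0.94^30 = 15.6% in the extreme case.

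*For scale.* The exact 95% interval is 7.7% to 38.6% for 6 of 30 and 2.1% to 26.5% for 3 of 30. The illustrated shifts lie inside the sampling uncertainty of one group. That interval, however, is centred on the observed rate and does not allow for bias.

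**The case against.** The strongest reply is that much of this is already handled. All medication must be listed, rescue use must be on the CRF, each adverse event record includes treatment, and Table 7-3 uses need for medication when grading severity. The solicited diary works by day, so dates match its resolution. A subject who feels feverish, measures, and then takes a tablet is captured by the highest-reading rule. To turn a febrile subject into a non-case over the whole course, masking must also hide every qualifying reading over 7 × 2 = 14 required evenings. The diary card itself is not among the documents, and extra tables may sit in an analysis plan that is not shown.

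Most of this stands, and it rules out several stronger readings that a reader might infer:

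- *That analgesics are wholly without limit.* Acetylsalicylic acid beyond 14 days is prohibited.
- *That drug timing is not captured.* Day-level timing is foreseen, although the field list is permissive. Only the time of day and the tie to the reading are absent.
- *That reactogenicity is in fact understated.* No event, usage or masking rate is given, so only the possibility is supported.
- *That pain and headache rates are lost as fever rates may be.* Treating a symptom does not erase its occurrence. Only preventive use or reduced intensity matters here.
- *That a true dose difference would be flattened.* No test between doses is planned. Nothing shows that subjects on the higher dose would medicate more, and open-label awareness could equally raise symptom reporting.

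What the reply does not meet is the specific gap. The highest-reading rule helps only if the subject happens to measure before the tablet, and nothing asks for that. How fever is tabulated can be left to an analysis plan. What the diary collects cannot.

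**Conclusion.** The concern holds in limited form. Apart from prolonged acetylsalicylic acid, analgesic and antipyretic use around each vaccination is unrestricted. One evening temperature is required, and fever is counted with no provision for a reading taken under an antipyretic. Reported fever at each dose can therefore be too low, and pain-type intensity can be too low to a lesser degree.

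Under the simple model the bias within a group can only be downward. Its size is unknown: on the assumed ranges it runs from a negligible 3% to 40% in relative terms, and the fall from 20% to 10–15% is an illustration, not an estimate. The point does not call into question which drugs are permitted, which is a clinical matter. It is a cheap improvement to data collection, and worth making before enrolment because the information cannot be rebuilt afterwards.

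**What to change.** Leave the permitted drugs as they are.

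1. **Section 7.3.4.1 and the diary, Days 0–6 after each dose.** Ask subjects to take and record a temperature before any analgesic or antipyretic where possible. The existing highest-reading rule then captures it.
2. **Same diary days.** Add one daily line: whether such a drug was taken, at what time, and whether for prevention or for a symptom.
3. **Section 10.3.2.** Report the percentage using such drugs at each dose. Beside fever as recorded, give a sensitivity count of subjects with a temperature of 37.5°C or above or an antipyretic taken for feverishness.

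The cost is a slightly longer diary and one extra table. The sensitivity rate may be somewhat too high, because some subjects who treat feverishness would never have reached 37.5°C. It should therefore be read together with the recorded rate and not replace it.

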### 6.5.2. Prohibited treatment

The following medications are prohibited during this clinical study:

- (1) The following treatments are prohibited until 30 days after the second vaccination:
  - Other vaccine
  - Immunoglobulins

- Any blood products
- Immunosuppressants or other immunomodulators\*
  - \* For corticosteroids, this includes prednisone  $\geq 0.5$  mg/kg/day or equivalent. Inhaled and topical steroids are allowed.
- Chronic or long-term (defined as  $> 14$  days) use of acetylsalicylic acid medication

(2) The following treatments are prohibited during the study period:

- Investigational/non-registered product (including drug, vaccine and invasive medical device)

Subjects who have received these prohibited treatments should be withdrawn from this trial.

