### **4.3. Criteria for treatment discontinuation or removal from the study**

#### **4.3.1. Withdrawal criteria**

Discontinuation from study is defined as discontinuation of all study visit and examinations. Participants may voluntarily withdraw from the study for any reason at any time. They may be considered withdrawn if they state an intention to withdraw, or fail to return for visits, or become lost to follow up for any other reason. Generally, subjects must be withdrawn from the study for any of the following reasons:

- (1) Subject consent withdrawal.
- (2) Lost to follow-up
- (3) Administration of prohibited medication/treatment/vaccine listed in [Section 6.5.1](#).
- (4) Any pathological event, clinical adverse event, or any change in the subject's status giving indication to the physicians that further participation in the study may not be the best interest of the subject.

These criteria should be checked at each visit subsequent to the first visit and before any study related activity has been conducted. All subjects enrolled will be followed till Day 210. Protocol violations should not lead to subject withdrawal unless they indicate a significant risk to the subject's safety.

If any subject discontinues the study prematurely, the investigator must determine the primary reason for a subject's premature withdrawal and record this information in the medical chart and Off Study Form. For those who are withdrawn due to adverse event(s) or serious adverse event, the event should be followed until resolution or the event is considered stable.

A final safety follow-up conducted through telephone call(s) should be arranged for these subjects as soon as possible. However, for a subject withdrawn within the regular study visit as a reason other than AE, the telephone follow-up could be omitted and no further information has to be collected since last visit (see [Section 5.6](#)). Moreover, for those who are lost to follow-up, investigators should make every effort to contact the subjects and document the steps taken, such as dates of telephone calls, in the source documents.

Subjects who are prematurely withdrawn from the study will not be replaced by an equal number of newly enrolled subjects.

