## **16. Protocol Deviations**

All deviations from the protocol should be reported to NHRI Vaccine Research and Development Center. This includes but is not limited to the following:

1. Subjects who entered the study even though they did not satisfy the entry criteria;
2. Subjects who developed withdrawal criteria during the study but were not withdrawn;
3. Subjects who received the wrong treatment or incorrect dose;
4. Subjects who received concomitant treatment in an incorrect manner.

Additionally, exceptions or deviations that could conceivably affect the collection or interpretation of data related to safety or efficacy assessments should also be reported. Examples include subject noncompliance with medication, surreptitious use of medications prohibited by the protocol, inability or unwillingness to accurately report adverse events or concomitant medication use.

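### Withdrawal after any prohibited treatment ends follow-up that the whole-study safety endpoint needs, and sits against Section 4.3.1's own limit on withdrawal for violations

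*Protocol*

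**What the plan says.** Section 6.5.2 bans one list of treatments up to 30 days after dose 2, and investigational products for the whole study. It ends: "Subjects who have received these prohibited treatments should be withdrawn from this trial".

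Section 4.3.1 opens with a definition: "Discontinuation from study is defined as discontinuation of all study visit and examinations". Its list of reasons begins "Generally, subjects must be withdrawn from the study for any of the following reasons", and item (3) is "Administration of prohibited medication/treatment/vaccine listed in" Section 6.5.1. That section covers permitted treatment; 6.5.2 is meant. Synopsis VII.3 carries the same item (3). Section 16 counts as a deviation "Subjects who developed withdrawal criteria during the study but were not withdrawn".

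Section 4.3.1 also states "All subjects enrolled will be followed till Day 210" and "Protocol violations should not lead to subject withdrawal unless they indicate a significant risk" to the subject's safety.

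After withdrawal the plan provides one telephone call with the Visit 7 procedures and no blood sample. Sections 4.3.1 and 5.8 let the call be omitted when a subject leaves at a regular visit for a reason other than an AE. Footnote # to Table 5-1 and the synopsis flow chart drops the regular-visit condition. For a subject withdrawn because of an AE or SAE, "the event should be followed until resolution or the event is considered stable".

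**The concern.** The primary endpoint in Section 9.1 includes all AEs and SAEs over the entire study period. Receiving a banned treatment gives no reason to stop looking for them, and the subject has already been vaccinated. The withdrawal rule stops that search. Before Visit 5 it also removes blood tests that feed the secondary endpoints.

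The loss may be related to safety. Section 6.6 allows rescue medication for post-vaccination symptoms, and systemic prednisone at or above 0.5 mg/kg/day is banned under 6.5.2. A subject treated in this way for a reaction therefore meets the withdrawal rule. Withdrawn subjects are not replaced, and Section 10.5 applies no missing-data method.

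**Working it through.** **1. The rules side by side.** Receiving a prohibited treatment is a violation; Section 16 item 4 lists incorrect concomitant treatment as a deviation. Under 4.3.1(3), 6.5.2 and synopsis VII.3(3) it leads to withdrawal. Under the later sentence in 4.3.1 it should not, unless safety is at significant risk. Section 4.3.2 lets subjects stay on after a dosage deviation or an off-schedule second dose, but does not mention prohibited treatment. A site that keeps the subject in meets Section 16 item 2. A site that withdraws the subject sets aside the 4.3.1 sentence.

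**2. Does withdrawal protect an analysis?** Sections 10.1.2 and 10.1.3 already exclude major violators from the ATP cohorts. The timed ban ends on Day 21 + 30 = 51, or Day 24 + 30 = 54 if dose 2 is given at the end of its window. The last titre sample is on Day 42 (39 to 45). The ban therefore outlasts it by 51 − 42 = 9 days, with a range of 51 − 45 = 6 to 54 − 39 = 15. Treatment first taken after that sample cannot affect a titre.

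**3. Loss per withdrawn subject.** Inputs from Table 5-1: safety laboratory at Visits 1, 3 and 5; titres at Visits 2, 4 and 5; epitope mapping at Visits 2 and 5; end of follow-up on Day 210. Days lost = 210 − day of withdrawal.

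| Withdrawal | Laboratory draws lost | Titre samples lost | Post-vaccination epitope sample | Days without new-event collection |
|---|---|---|---|---|
| Day 7 | 2 of 3 | 2 of 3 | lost | 203 (96.7%) |
| Day 24 | 1 of 3 | 1 of 3 | lost | 186 (88.6%) |
| Day 42, after Visit 5 | 0 | 0 | kept | 168 (80.0%) |
| Day 51 | 0 | 0 | kept | 159 (75.7%) |

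After a Day 21 dose the unsolicited-event window is Days 21 to 41, so withdrawal on Day 24 loses Days 25 to 41, or 17 of 21 days.

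These are worst cases. They assume that treatment, detection, withdrawal and any final call fall on the same day. Withdrawal criteria are scheduled for checking at Visits 2, 3, 4, 5 and 6, so some cases would surface later and lose less. After Visit 5 the lost time was to be covered by only two telephone calls.

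**4. Effect on an arm.** Table 6-1 gives 1 + 1 + 3 + 25 = 30 for A05 and 0 + 1 + 4 + 25 = 30 for B10, so one subject is 1/30 = 3.3%. The protocol gives no rate of prohibited treatment, so assume 1 to 3 withdrawals per arm and count them as contributing nothing. With no events in n subjects, the exact two-sided 95% upper limit is 1 − 0.025^(1/n). The chance of seeing at least one event with a true 5% rate is 1 − 0.95^n.

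| n | Upper limit for 0/n | Chance of at least one event |
|---|---|---|
| 30 | 11.6% | 78.5% |
| 29 | 11.9% | 77.4% |
| 27 | 12.8% | 75.0% |

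If the withdrawn subject stays in the Total Vaccinated cohort denominator, an unobserved later event counts as no event.

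**The case against.** The best counter-argument is that the plan has a rule one can find. The withdrawal instruction appears in 4.3.1(3), 6.5.2 and synopsis VII.3(3), and Section 16 backs it. The sentence on violations is general and may be meant for deviations that are not on the list. The Day 210 statement may describe planned duration only. This is a fair reading, and it answers anyone who infers that sites could not work out what to do. It settles which rule governs, but the rule that wins is the one that discards follow-up.

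Four other stronger inferences are not supported:

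- **A treated reaction drops out of sight.** It does not. An event that causes withdrawal is followed to resolution or stability, and 7.3.5.2 has AEs followed to Day 210 by visit or telephone. What is missing is any provision to look for new events after the final contact.
- **The main Day 42 titre analysis loses data.** Mostly it does not. The synopsis names ATP as the efficacy population, and a subject treated before Visit 5 would usually be an ATP immunogenicity exclusion anyway. Continued sampling mainly restores values to the Total Vaccinated cohort.
- **Most of the 210 days is lost in every case.** The percentages in the working are upper bounds.
- **The steroid ban is wrong because it has no minimum duration, unlike entry criterion 13.** A stricter on-study rule than a six-month look-back is an ordinary choice.

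It is also true that entry criteria 10 to 14 screen out planned use, and that the primary analysis is descriptive. Both limit the practical effect.

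**Conclusion.** The point holds as an avoidable loss of safety follow-up, together with wording in 4.3.1 that pulls two ways. The certain part is textual: withdrawal for this reason ends scheduled collection of new AEs and SAEs, and before Visit 5 it also ends safety laboratory, titre and epitope sampling. The size is modest. Under the assumed 1 to 3 withdrawals per arm, the upper limit for an unseen event moves from 11.6% to at most 12.8%, and no planned conclusion would change. The case for acting is that withdrawal is not needed for any analysis, the subjects concerned may include some who were treated for reactions, and the remedy uses contacts already in the schedule. A statistical analysis plan could not repair this, because the rule decides whether the data are collected at all.

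**What to change.** - In 4.3.1, 6.5.2 and synopsis VII.3, take prohibited treatment off the withdrawal list. State that it is a deviation that ends further vaccination but not study participation. Section 16 item 4 still captures it.
- In 4.3.2 and the synopsis, add receipt of a prohibited treatment before dose 2 as a contraindication to the second vaccination. Without this, removing item (3) would weaken a safeguard.
- Unless consent is withdrawn, continue all remaining visits, blood samples, diary cards and calls to Day 210, including the Visit 4 sample and diary return when dose 2 is not given.
- Keep the subject in the Total Vaccinated cohort. Exclude from the ATP immunogenicity cohort only samples taken after the treatment.
- Align 4.3.1, 5.8 and footnote # (Table 5-1 and the synopsis flow chart) on when the final call may be omitted.
- Correct the reference in 4.3.1(3) from 6.5.1 to 6.5.2.

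The cost is amendment wording and, for each affected subject, a few visits or calls that were already planned.
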